## 4.2 Randomisation

In order to reduce bias and the influence of any difference in the baseline characteristics between the three groups, we have chosen to randomise the allocation of subjects. This aims to achieve a balance between the three groups in any important confounding factors such as levels of pre-existing antimycobacterial immunity (influenced by, for example, country of origin and length of time elapsed since prior BCG vaccination). This will be performed by variable block randomisation using sequentially numbered sealed envelopes, prepared by an independent colleague at the Centre for Statistics in Medicine, to ensure allocation concealment. Volunteers are blinded as they will receive a paired placebo at the same time of vaccination. The bronchoscopist will be blinded to the route of vaccine administration. This is intended to eliminate any bias in the reporting of the appearance of the lung mucosa and extent of airway inflammation. In addition, the postdoctoral researcher in the laboratory overseeing the immunological analyses will also be blinded to reduce any bias that could be introduced at the sample processing stage. All samples will be anonymised.

## 4.3 Vaccine dosage

Trials of MVA85A to date have established  $1 \times 10^8$  pfu as the optimal dose for intradermal injection in adults. There are no published studies of dose-response via the mucosal route of vaccination. Although the fractional delivered dose of aerosolised viral vectored vaccines to the mucosal surface may be considerably less than 25%, there is evidence that strong mucosal and systemic immune responses, comparable to the injectable route, are nevertheless achieved (64, 65). The first aerosol safety study (TB026) was completed using  $1 \times 10^7$  pfu MVA85A with no severe or serious adverse events.

In this trial we will dose escalate to a medium dose to further evaluate safety and immunogenicity. The first volunteer in the study will receive a dose of  $5 \times 10^7$  pfu MVA85A by the aerosol route. This volunteer will be vaccinated ahead of any other volunteers and the profile of adverse events will be examined. No other volunteers will be vaccinated until at least 48 hours has elapsed following the first volunteer being vaccinated. The Chief Investigator will then decide whether it is safe to proceed to vaccinate the remaining volunteers post review of this safety data. The Chair of the Local Safety Committee will be informed if an untoward adverse event profile occurs that differs from past experience with MVA85A.

### Restart of enrolment into Group 2

When restarting enrolment into group 2 of the trial, the first participant will be enrolled, and no further enrolment will take place until they have received their second bronchoscopy. A second volunteer will then be enrolled and once they have received their second bronchoscopy, providing there are no safety concerns, enrolment will continue as normal.

### Time points

#### *Prior BCG – trial enrolment time window*

The specified period for prior receipt of BCG is such that no less than six months must have elapsed between prior BCG vaccination and subsequent trial enrolment. This is to allow for the peak BCG-induced immune response to have occurred, which is usually around 2-4 weeks post BCG vaccination.

#### *Screening – trial enrolment time window*

Enrolment should take place no longer than 120 days following the date of screening appointment. If more than 120 days elapse, the screening visit should be repeated in full prior to enrolment in order to minimise the risk to participants of any new unidentified health problems having arisen during that period.

#### *Follow up period*

The follow up period will be five months from the last vaccination (i.e. 24 weeks from enrolment), in accordance with findings from previous trials in which adequate safety data and reliable markers of immunogenicity have been obtained in this time interval.

## **4.4 Risks and Benefits**

### **Potential risks**

The potential risks to participants in this trial include risks associated with:

#### **1. Venepuncture and intravenous cannulation**

Localised bruising and discomfort can occur at the site of venepuncture. Infrequently fainting may occur. The total volume of blood drawn over a six month period will be 586 mL which should not compromise the health of these healthy individuals.

An intravenous cannula is routinely inserted into a peripheral (usually forearm) vein prior to bronchoscopy to administer intravenous sedation, and removed once the procedure is completed. The risks of cannulation are identical to those associated with venepuncture. Additionally cannulation carries a small risk of soft tissue infection which will be minimised by an aseptic insertion technique and is easily recognisable and treatable. The short duration of cannulation (a few hours) further minimises this risk.

#### **2. Vaccination**

MVA85A has undergone thorough pre-clinical testing and has now been administered to over 2300 healthy human individuals with no serious adverse events. The potential known adverse events associated with vaccination are:

##### *Local reaction from intradermal vaccination*

The typical local reaction as a result of intradermal injection is temporary pain, redness and swelling at the site of the injection with a 5-10 mm central red swollen area and a paler red area ranging from 5-10 mm in diameter which peaks at 48 hours post vaccination. At seven days post vaccination, only the central area of redness remains. This fades over a few weeks and is not usually apparent eight weeks after vaccination. Scaling occurs as part of the healing process, and itching is possible.

##### *Local reaction from aerosol inhaled vaccination*

Enrolment for the first ever trial administering a virally vectored vaccine by the aerosol route has just been completed in our group. The trial was single blinded paired placebo, so all volunteers received either an intradermal vaccine with saline by aerosol or vice versa. There was no significant difference between systemic adverse events, respiratory adverse events or pulmonary function tests between the two groups.

Constitutional influenza-like symptoms such as fatigue, headache, malaise, feverishness, and muscle aches can occur with any vaccination lasting for 2-3 days. In the case of MVA85A, fatigue and headache are most common, occurring in 50-90% of subjects, and these are nearly always mild. Presyncopal and syncopal episodes may occur at the time of vaccination which rapidly resolve. As with any other vaccine, temporary ascending paralysis (the Guillain-Barré syndrome, GBS) or immune mediated reactions that can lead to organ damage may occur. For influenza vaccines an excess of approximately 1 GBS case per million persons immunized has been observed. No cases were observed in people under 45 years of age. However, this has never been seen with the MVA85A vaccine or vaccines containing any of its components.

##### *Allergic reactions*

Allergic reactions from mild to severe may occur in response to any constituent of a vaccine preparation. Anaphylaxis is extremely rare but can occur.

### **3. Bronchoscopy**

Bronchoscopy is a widely and safely used investigative procedure in clinical research studies involving both healthy subjects and subjects with respiratory conditions such as asthma and interstitial lung disease (58, 59). Clinical guidelines for performing investigative bronchoscopy in research studies are well established (60). In 98% of cases subjects have no memory of the procedure.

The bronchoscopies will be carried out in a dedicated NHS bronchoscopy suite with an excellent safety record by highly skilled and experienced respiratory physicians. Intravenous sedation and local anaesthesia are administered prior to bronchoscopy to reduce discomfort, facilitate the procedure, and remove memory of the event. Trained, experienced staff and facilities for resuscitation and drugs for reversal of sedation will be available. No transbronchial or endobronchial biopsies will be taken. To further minimise risk, subjects will be excluded if they have an abnormal chest x ray, a significant smoking history, or any evidence of lung disease, including asthma (as defined by: a clinical diagnosis of asthma; prescription of asthma medication; airflow obstruction on spirometry; history of nocturnal or exercise-induced wheeze).

The risks of bronchoscopy are: infection secondary to bronchoalveolar lavage, bleeding, and respiratory depression secondary to sedation:

- Bronchoalveolar lavage is a routine procedure in investigative bronchoscopy and carries minimal bleeding risk. The risk of infection or febrile reactions will be minimised by full bronchoscope asepsis and superflush.
- Respiratory depression secondary to sedation is rare. No rescue medication for oversedation has been required in a 3 year audit period and sedation with midazolam and fentanyl removed memory of the event in over 98% of subjects (internal audit data).
- Allergic reactions from mild to severe may occur in response to any constituent of the local anaesthetic or sedative agents. Anaphylaxis is extremely rare but can occur.

The Summary of Product Characteristics (SmPC) for the local anaesthetic and sedative agents contain full details of the indications and side effects of these licensed medications.

Bronchoscopies were well tolerated in the volunteers of the recently completed Phase I trial TB026. No serious adverse events were reported during or as a result of bronchoscopy.

### **4. Chest X-Ray**

A chest x-ray is a painless routine radiological investigation which exposes subjects to approximately 0.02 milliSieverts of radiation, equivalent to around three days of natural background radiation. The additional risk of cancer due to one chest x ray is extremely small, approximately 1 in 900,000.

### **5. Pulmonary Function Tests**

Vigorous respiratory manoeuvres such as forced expiration through the spirometer can occasionally lead to coughing or lightheadedness, but these symptoms are mild and rapidly self-limiting.

#### **Known potential benefits**

Subjects are not expected to benefit directly from participation in this trial. Subjects will gain some information about their general health as a result of the screening history, examination, blood tests, urine tests, chest x-ray, and pulmonary function tests. They may also gain health information from the bronchoscopy. It is hoped that their contribution will enable the development of a safe and successful vaccine for TB and further our knowledge about mucosal vaccines.

## **4.5 Data Collection**

The bronchoscopic procedure is not being assessed for safety as it is a standard medical technique with a known profile of expected risks as described in section 4.4. Vaccination safety data for both routes will be collected both actively and passively as follows:

- Information about local and systemic adverse events will be collected at each visit by medical history, examination and measurement of the injection site, pulmonary function testing, bronchoscopic examination of the lungs, and the use of diary cards.
- Vital signs will be recorded at each visit.
- Safety blood tests (FBC, LFT, U&E) will be collected at screening and day 7.

This information will be entered into the CRF contemporaneously at each visit. Results of laboratory investigations and immunological data will be entered into the CRF. The CRFs will be the source data for this trial.

## **4.6 Duration of Study**

Volunteers will all be followed up to week 24, with clinic visits and blood test as outlined in table 1.

## **4.7 Definition of start and end of the trial**

The start of trial is defined as the date of the first vaccination of the first volunteer. The end of trial is the date of the last visit of the last volunteer.

## **4.8 Discontinuation of the trial**

The trial will be discontinued in the event of any of the following:

- New scientific information is published to indicate that subjects in the trial are being exposed to undue risks as a result of administration of the IMP, or as a result of the trial procedures or follow-up schedule.
- Serious concerns about the safety of the IMP arise as a result of one or more vaccine related SAE(s) occurring in the subjects enrolled in this or any other on-going trial of the MVA85A vaccine.
- For any other reason at the discretion of the Chief Investigator.

# **5 SELECTION AND WITHDRAWAL OF SUBJECTS**

## **5.1 Inclusion Criteria**

Subjects must meet all of the following criteria to enter the trial:

- Healthy adult aged 18-55 years
- Resident in or near Oxford for the duration of the trial period
- No relevant findings in medical history or on physical examination
- Confirmation of prior vaccination with BCG not less than 6 months prior to projected trial vaccination date (by visible BCG scar on examination or written documentation)
- Allow the Investigators to discuss the individual's medical history with their GP

- Use effective contraception for the duration of the trial period (females only)
- Refrain from blood donation during the trial
- Give written informed consent
- Allow the Investigator to register subject details with a confidential database to prevent concurrent entry into clinical trials
- Able and willing (in the Investigator's opinion) to comply with all the trial requirements

## **5.2 Exclusion Criteria**

Subjects must meet none of the following criteria to enter the trial:

- Any respiratory disease, including asthma
- Current smoker
- Clinically significant abnormality on screening chest x-raya
- Clinically significant abnormality of pulmonary function testsa
- Any nasal, pharyngeal, or laryngeal finding which precludes bronchoscopy
- Current use of any medication taken through the nasal or inhaled route including cocaine or other recreational drugs
- Laboratory evidence at screening of latent *M. tb* infection as indicated by a positive ELISPOT response to ESAT6 or CFP10 antigensb
- Clinical, radiological, or laboratory evidence of current active TB diseasea
- Previous vaccination with candidate vaccine MVA85A or candidate vaccine FP85A or any other recombinant MVA vaccine
- Clinically significant history of skin disorder, allergy, atopy, immunodeficiency (including HIV), cancer (except BCC or CIS), cardiovascular disease, gastrointestinal disease, liver disease, renal disease, endocrine disorder, neurological illness, psychiatric disorder, drug or alcohol abuse
- History of serious psychiatric condition
- Concurrent oral or systemic steroid medication or the concurrent use of other immunosuppressive agents
- History of anaphylaxis to vaccination or any allergy likely to be exacerbated by any component of the trial vaccine, sedative drugs, or any local or general anaesthetic agents
- Any abnormality of screening blood or urine tests that is deemed to be clinically significant or that may compromise the safety of the subject in the triala
- Positive HBsAg, HCV or HIV antibodiesa
- Female currently lactating, confirmed pregnancy or intention to become pregnant during trial period
- Use of an investigational medicinal product or non-registered drug, live vaccine, or medical device other than the trial vaccine for 30 days prior to dosing with the trial vaccine, or planned use during the trial period
- Administration of immunoglobulins and/or any blood products within the three months preceding the planned trial vaccination date
- Any other significant disease, disorder, or finding, which, in the opinion of the Investigator, may either put the subject at risk or may influence the result of the trial or may affect the subject's ability to participate in the trial

aSubjects who are excluded from the trial because they have been discovered during screening procedures to be suffering from a previously undiagnosed condition thought to require further medical attention will be referred appropriately to their GP or an NHS specialist service for further investigation and treatment.

bSubjects discovered to have evidence of latent *M. tb* infection as defined by a positive ELISPOT test will be referred for a plain chest x-ray and reviewed with the TB nurse specialists and considered for chemoprophylaxis. If there is any evidence of active TB disease either on clinical or radiological grounds, further investigation and treatment will be offered under the supervision of a consultant physician in respiratory or infectious diseases.

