| Chief Investigator             | [name]                                                                                                                                                                                                                                                                                                                                                                                                    |
| Trial Centres                  | Centre for Clinical Vaccinology and Tropical Medicine (CCVTM), Churchill Hospital, [name]
& Oxford Centre for Respiratory Medicine, Oxford University Hospitals NHS Trust                                                                                                                                                                                                           |
| Planned Trial Period           | Prospective start date for screening August 2013                                                                                                                                                                                                                                                                                                                                                                      |
| Trial Duration                 | Estimated at 18 months                                                                                                                                                                                                                                                                                                                                                                                                |
| Primary Objectives             | Safety of 5 x 10  pfu dose of MVA85A administered by aerosol and compared to the same dose administered intradermally                                                                                                                                                                                                                                                                                     |

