A problem with all virally-vectored vaccines including MVA85A is that individuals build up immunity to the virus base (anti-vector immunity) which makes the vaccine less efficient and not suitable for re-use within short time frames. An important potential advantage of mucosal immunisation, in addition to the ones mentioned thus far, is that aerosol vaccination may minimise or avoid induction of systemic anti-vector immunity and allow homologous boosting with the same viral vector; thus minimising cost of vaccine development (28-30). Furthermore, for some vectors, e.g. human Adenovirus serotype-5, up to 80% of adults have antibodies to AdHu5 and this pre-existing immunity significantly limits the utility of this vector (31-34). Our hypothesis is that mucosal immunisation with MVA85A does not result in induction of systemic anti-vector immunity. Recent work in nonhuman-primates by our collaborators at the Health Protection Agency, comparing 2 routes of administration, showed anti-MVA antibody responses are seen in intradermally vaccinated animals but not in animals given MVA85A by aerosol (Figure 2; (35))

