#### Description and pre-clinical experience of MVA and MVA85A

Modified vaccinia virus Ankara (MVA) is a highly attenuated strain of vaccinia virus which cannot replicate in human cells. It is known to be highly immunogenic and is therefore suitable for use as a viral vector in new vaccine development. It has an excellent safety record as it was administered intradermally to approximately 120,000 people during the smallpox eradication campaign (38-41), and has since been used in numerous clinical trials of candidate vaccines against viral, mycobacterial and protozoal infections (42, 43). Meanwhile recombinant MVA vaccines administered by respiratory mucosal and gut mucosal routes have demonstrated strong immune responses in both rodents and non-human primates (44).

Antigen 85A is a highly conserved antigen expressed by *M. tb*, BCG, and all other mycobacterial species sequenced to date. It is a 32-kDa protein, and is an enzyme, mycolyl transferase, which is involved in cell wall biosynthesis (45). Antigen 85A is highly immunodominant in both animal and

human studies (46-48), and protects against *M. tb* challenge in mice, guinea pigs and non-human primates (49, 50). The recombinant MVA85A vaccine incorporates the 1176 base pair gene for antigen 85A into the viral DNA allowing expression of this secreted antigen.

Experiments in mice, guinea pigs, cattle, and non-human primates have shown that a prime-boost schedule of vaccination with BCG followed by MVA85A, either intradermally, intramuscularly or mucosally, can improve protective efficacy against subsequent *M. tb* challenge, compared to BCG alone (10, 50-52). A mouse GLP toxicity study using the intradermal route of administration revealed no differences from PBS-injected controls apart from irritation at the site of administration. An additional mouse GLP toxicology study of aerosol administration revealed no differences from controls given aerosolised PBS.

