| Secondary Objectives
To characterise mucosal and systemic immunogenicity of viral vector (MVA) and insert (Ag85A) by comprehensive characterisation of humoral and cellular immune responses

Evaluate functional relevance of anti-vector immunity induced by aerosol and systemic immunisation in MVA85A-prime followed by homologous MVA85A-boost administered 4 weeks after the MVA85A-prime | 

1. Induction of humoral and cell-mediated immunity to MVA by aerosol and systemic immunisation

2. Induction of cell-mediated and humoral immunity to Ag85A by aerosol and systemic immunisation

3. Effect of a boosting immunisation one month after prime on humoral and cell-mediated immunity to insert (Ag85A) and vector (MVA)

 |

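### Section 5.2 bars earlier recombinant MVA vaccines but not smallpox/vaccinia or non-recombinant MVA vaccination, which adds avoidable variance and chance imbalance to the secondary anti-vector comparisons

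*Protocol*

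**What the plan says.** **Eligibility.** Section 5.1 admits "Healthy adult aged 18-55 years", and section 1 gives "Prospective start date for screening August 2013". Section 5.2 excludes "Previous vaccination with candidate vaccine MVA85A or candidate vaccine FP85A or any other recombinant MVA vaccine". The other vaccine limits are short: the live-vaccine exclusion in section 5.2 covers 30 days before dosing, and the postponement rule in section 5.4 covers three weeks. The last bullet of section 5.2 lets the investigator exclude for any other significant finding thought capable of influencing the trial's result.

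**The vector.** Section 2.1 states: "Modified vaccinia virus Ankara (MVA) is a highly attenuated strain of vaccinia virus which cannot replicate in human cells". It adds that "it was administered intradermally to approximately 120,000 people during the smallpox eradication campaign". Writing about the human adenovirus vector AdHu5, the same section says that "this pre-existing immunity significantly limits the utility of this vector".

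**The endpoint.** The first secondary outcome in section 3 is "Induction of humoral and cell-mediated immunity to MVA by aerosol and systemic immunisation". A secondary objective is to evaluate the functional relevance of that immunity in the prime-boost regimens. Avoiding anti-vector immunity is also in the trial's title.

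**Screening and analysis.** Section 7.2 takes a general medical history, with corroboration from the GP where possible, and separately collects demographic and occupational data on TB exposure. Table 1 schedules exploratory immunology blood at screening and day 0. Section 4.2 randomises in variable blocks with no stated stratification and gives pre-existing antimycobacterial immunity as an example of a confounder. Section 9.1 compares one-week and six-month responses between the three groups, adds an area-under-curve comparison over all time points, and plans paired within-group tests.

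**The concern.** The criterion shows an intention to keep out people who have already met the vector. The word *recombinant* then leaves out two sources of such exposure that follow from section 2.1: vaccinia vaccines, because MVA is a vaccinia strain, and the non-recombinant MVA of the smallpox campaign.

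A volunteer with such a history may carry immunity to the vector at day 0. The first dose would then recall a response instead of inducing one, and could act differently on the Ag85A response. If such volunteers fall unevenly across three arms of 12, the comparison of aerosol with intradermal priming on anti-vector immunity becomes noisier and can be shifted in either direction by chance.

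**Working it through.** **1. Does any criterion stop such a volunteer?** Take a 55-year-old screened in August 2013, born between about August 1957 and August 1958, who had a childhood smallpox vaccination.

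- Vector bullet in 5.2: not met, since the vaccine was neither MVA85A, FP85A nor a recombinant MVA.
- Live-vaccine bullet in 5.2: not met, since the vaccination lies decades outside the 30 days.
- Postponement rule in 5.4: not met, for the same reason.
- Catch-all in 5.2: applies only if the investigator learns of the vaccination and judges it relevant.
- Screening in 7.2: a general history may bring it out, but no item asks for it.

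Entry is therefore possible and nothing ensures that it is noticed. The same holds for someone given non-recombinant MVA.

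**2. Is it handled later?** Section 4.2 names no stratification factor. Section 9.1 does not name baseline vector immunity as a covariate or as a subtraction in the between-group comparisons. The area-under-curve analysis uses all time points but is described as comparing overall responses, not change. The paired tests work within a group, and their pairs are not specified.

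**3. Does the plan's own sample size cover this?** Section 9.1 gives 12 volunteers for 80% power on the summed 85A peptide pools. This cannot be reproduced, because no standard deviation, significance level or sidedness is stated. It concerns the 85A ELISPOT and not immunity to MVA, so the point does not depend on it.

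**4. How likely is a chance imbalance?** Inputs: 12 per arm and 36 in total (section 9.1), and the share *p* of enrolled volunteers with earlier exposure, which the documents do not give. Assumed values: 5%, 10% and 20%.

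Let X1 and X2 be the exposed counts in two given arms, independent Binomial(12, *p*), with f(k) the probability of k exposed. Then

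P(|X1 − X2| ≥ 2) = 1 − Σ f(k)² − 2 Σ f(k) f(k+1).

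| *p* | Expected per arm, 12*p* | P(equal) | P(differ by 1) | P(differ by 2 or more) |
|---|---|---|---|---|
| 5% | 0.6 | 0.419 | 0.440 | 0.142 |
| 10% | 1.2 | 0.282 | 0.429 | 0.289 |
| 20% | 2.4 | 0.204 | 0.358 | 0.438 |

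The chance that at least one of the 36 is exposed is 1 − (1 − *p*)^36, which gives 0.84, 0.98 and over 0.99. The chance that some pair among the three arms differs by two or more is 0.27, 0.52 and 0.71.

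**The case against.** The case against is substantial, and parts of it stand.

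- **The endpoint is induction, not level.** Blood is drawn at screening and day 0, so a rise above baseline can be measured in an exposed volunteer too. Figure 2, the macaque precedent headed as anti-vaccinia IgG, is itself plotted as change from the prevaccination level. This stands, and it limits the harm. It does not remove it: a recall response is not a primary response even after subtraction, and section 9.1 does not name the baseline in its between-group comparisons.
- **Randomisation protects against baseline differences, and section 4.2 offers antimycobacterial immunity only as an example.** This also stands: no systematic bias is expected. What remains is chance imbalance, which is not small at 12 per arm.
- **The catch-all and the general history could pick it up.** They could, but one is discretionary and the other has no specific question.
- **How baseline immunity enters the model is commonly SAP content.** That is fair for the analysis. A SAP cannot change who is eligible, and if the history is not recorded it would have to rely on the baseline assay alone.

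Two stronger readings are tempting and should not be drawn. A reader might infer that the anti-vector hypothesis cannot be assessed at all in an exposed volunteer, or that the comparison is invalid. The baseline sampling and randomisation do not support that. A reader might also fix the exposed share from the calendar of past smallpox vaccination. The documents give no date when routine vaccination stopped, no coverage and no age profile of recruits. The remark in section 2.1 that pre-existing immunity limits a vector concerns AdHu5, and no comparable figure is given for MVA.

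**Conclusion.** The gap is real and can be checked in the text. On the protocol's own description of MVA, section 5.2 lets in people with earlier exposure to the vector's parent virus, in a trial whose first secondary outcome is immunity to that vector. The effect is added variance and chance imbalance in the secondary anti-vector comparisons. The primary safety objective is not directly affected, and section 9.1 calls the endpoints primarily descriptive.

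The size is unknown from the documents. The 14% to 44% chance that two given arms differ by two or more exposed volunteers rests on an assumed exposure of 5% to 20% and on independent binomial counts. It measures how often an imbalance would occur, not how far it would move the result. The change is worth making because it is cheap, not because the trial fails without it.

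**What to change.** **Criterion.** Widen the bullet in section 5.2 to: *previous vaccination with MVA85A, FP85A, any MVA-based vaccine (recombinant or not) or any smallpox/vaccinia vaccine*. Add one specific question to the history in section 7.2.

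**Volunteers already enrolled.** Record smallpox vaccination history and measure anti-vector immunity in the baseline sample already drawn. Analyse the anti-vector endpoints as change from that baseline, or adjusted for it, in all volunteers. Add a sensitivity analysis that leaves out the exposed. The main analysis should keep all volunteers; restricting it to unexposed volunteers would shrink arms that are already small.

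**Cost.** One reworded bullet, one question, one baseline assay on existing samples, and a slightly smaller pool of older volunteers. The protocol is already at v4.1, after an amendment concerning boosts due from 2 September 2015, so the new criterion helps only remaining recruits. For everyone else the benefit comes from the recorded history and the baseline-adjusted analysis.
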